### Radiograph Eligibility Criteria

#### Inclusion Criteria

Eligible chest radiographs must meet all of the following criteria: it should (1) be of individuals aged 18 years or older; (2) be obtained either during the presence of respiratory symptoms or while the patient is undergoing treatment for a respiratory disease; (3) be any radiograph without a preexisting report at the time of inclusion; (4) be acquired on any X-ray equipment, provided that at least 1 frontal chest view is included; and (5) be performed either during the acute episode of the respiratory condition or throughout the postacute follow-up period, until its completion.

#### Exclusion Criteria

CXRs performed for peripherally inserted central catheter line positioning, preoperative risk assessment, lung cancer screening, or trauma-related evaluation will be excluded. In addition, radiographs printed on plain paper and examinations with technical quality below the minimum acceptable standard will also be excluded.

### Physicians

Radiograph interpretation will be performed by general practitioners or other nonradiologist physicians employed or otherwise engaged at participating trial sites. No restrictions will be imposed regarding age, sex, years since graduation, or previous training in imaging interpretation. All participating physicians will receive training using the study platform and must provide informed consent before contributing to interpretations. The training procedure emphasizes that AI outputs are advisory only; clinical responsibility remains fully with the interpreting physician, and AI suggestions never override clinical judgment. Afterward, they will complete a brief questionnaire assessing their baseline confidence in CXR interpretation, perceived challenges in reading CXRs, and initial impressions regarding the usability of the study platform (Multimedia Appendix 1).

### The LuAna Platform

LuAna is a cloud-based AI platform for CXR interpretation developed in partnership with the Brazilian Ministry of Health. The platform receives anonymized CXR with the accompanying physician report and generates 3 deep-learning outputs: (1) classification of images as normal or abnormal, (2) classification of specific radiologic findings (consolidation or pulmonary opacity, pneumothorax, atelectasis, pleural effusion, and cardiomegaly), and (3) probability scores for radiographic features suggestive of pulmonary TB. Operating fully in the cloud, LuAna provides decision support without requiring modifications to current imaging systems or clinical workflows.

### Data Collection

Anonymized data will be gathered using the LuAna platform (accessible on desktop or mobile), which records CXRs and physician interpretations (Figure 3). Physicians will access the platform using secure login credentials. All data will be automatically logged to enable auditing, reproducibility, and safety monitoring.

**Figure 3. F3:**
[figure not shown]
Workflow for chest X-ray (CXR) interpretation in control and intervention groups. Top panel (control group—without AI): CXRs from patients with respiratory complaints are interpreted solely by the physician (1), without access to AI support (2). Bottom panel (intervention group—with AI): physicians first perform an initial assessment of the CXR (1) and register their findings via the LuAna mobile app (2). After this, the AI model processes the image and returns a score and a heatmap highlighting abnormal regions (3). The physician can then review and, if needed, revise their interpretation based on the AI output (4). Both pre- and post-AI interpretations are recorded for analysis. For both groups, CXR assessments are compared against a reference standard, defined as thoracic radiologist evaluation performed on the CARPL, with reports independently double-validated by thoracic radiologists blinded to both the physician assessment and AI output. The primary outcome is the comparison of radiologic findings detection rates before and after AI assistance relative to the reference standard. The workflow includes data acquisition at the study centers, followed by radiologist annotation, primary and secondary end point evaluation, and statistical analysis at the coordinating center. AI: artificial intelligence; CARPL: Clinical Artificial Intelligence Research Platform for Labeling.

Only demographic variables, including age group, sex, and race, will be collected in aggregated form to characterize the study population and allow for fairness analyses, ensuring equitable and unbiased AI performance. CXRs will be captured either by photographing printed films positioned on a lit negatoscope, by photographing digital images displayed on a picture archiving and communication system monitor, or by direct screen capture, all following strict protocols to guarantee full anonymization. Physicians will capture only the thoracic image, ensuring that all patient identifiers are systematically removed and never visible. A patient ID entered solely to return the radiologist’s report to the local health unit will be encrypted and remain inaccessible to the research team. Nondiagnostic images or studies failing predefined quality-control criteria will be excluded from analysis.

Physicians will complete a brief questionnaire of their first CXR interpretation based on the following predefined questions: (1) Is the CXR normal or abnormal? (2) Are the specified radiological findings present or absent? and (3) Does the CXR show features suggestive of pulmonary TB? In the intervention group, after the physician’s clinical management, AI output (including probability scores and heatmaps) will be made available. Physicians will then document their final interpretation and decision-making process and subsequently record any changes made after reviewing the AI results. All data will be securely stored in encrypted, deidentified cloud-based repositories.

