### Ethical Considerations

This study was reviewed and approved by the local Ethics Committee of Hospital Israelita Albert Einstein (CEP Einstein), São Paulo, Brazil, registered under IRB00005041, in accordance with applicable national and international regulations (CAAE number 82494524.0.1001.0071). A waiver of written informed consent for patients was granted, as the study is strictly observational and involves no intervention in routine clinical care, no modification of clinical management, and no access to patients’ medical records. Only chest radiographs obtained as part of standard care were used, and all images were fully anonymized prior to storage and analysis, with no directly identifiable information included in the research dataset. However, written informed consent was obtained from the physicians responsible for enrolling patients in the LuAna trial, as they are considered direct research participants.

All data are handled under strict confidentiality procedures. Chest radiograph images were collected via the LuAna app and stored in an anonymized format on a secure cloud-based server.

The analytical database contains exclusively deidentified data. Access to identifiable information at the study sites, when applicable, is restricted to authorized local investigators. Study data will be securely stored at the hosting institution for a minimum of 5 years, in compliance with institutional and regulatory requirements.

Posttrial access pathways for the tool will be discussed with the Brazilian Ministry of Health to ensure continuity if the intervention proves beneficial. Technical details of the algorithm, including its development, training, validation, and performance characteristics, will be described in accordance with the CLAIM (Checklist for Artificial Intelligence in Medical Imaging) reporting guidelines [40], complementing the CONSORT-AI and SPIRIT-AI standards applied to the clinical trial components [32,33].

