#### Secondary Outcomes

The secondary outcomes are expected to demonstrate that AI assistance increases detection rates for each of the 5 radiographic findings, as well as overall pulmonary abnormality and TB-related patterns, relative to unaided physician interpretation. Improvements in abnormality localization accuracy are also anticipated, both for the AI outputs alone and for physician interpretations after reviewing AI results. Diagnostic performance compared with the reference standard is expected to improve, with higher sensitivity, specificity, AUC, positive predictive value, and negative predictive value, reflecting greater reliability in identifying clinically relevant radiological abnormalities. The secondary outcomes are depicted in Textbox 1.

Textbox 1.Secondary objectives and outcomes.Secondary objectivesMeasure the effect of artificial intelligence (AI) on physicians’ detection rates for each of the 5 radiologic findings independently, pulmonary abnormality, and features suggestive of pulmonary tuberculosisEvaluate AI algorithm performance in a real-world settingEvaluate physicians’ experiences regarding usability of the mobile interfaceAssess the impact of external influencing factors on AI algorithm predictionsEvaluate physicians’ learning related to interpretation of radiologic findings on chest X-rays (CXRs) before and after the interventionSecondary outcomesWhether the physician correctly identifies each of the 5 radiologic findings, pulmonary abnormality, and features suggestive of pulmonary tuberculosis on chest radiographsComparison between AI algorithm outputs for CXRs and thoracic radiologist reference standard classifications to calculate sensitivity, specificity, area under the receiver operating characteristic curve, positive predictive value, and negative predictive valueResponses to questions regarding the mobile app interface, responsiveness, and functionality measured using a 7-point Likert scaleAssociations between AI algorithm outputs for CXRs and CXR characteristics, including photo quality, presence of thoracic devices, and technical artifacts, as labeled by radiologistsChange in physician interpretation performance over time and according to the duration of participation in the study

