## Discussion

### Principal Findings

This trial is a pivotal effort to evaluate how AI can enhance diagnostic accuracy, clinical workflows, and physician performance in interpreting chest radiographs.

By using a batched stepped-wedge cluster-randomized design across a nationally representative sample of health care settings, we aim to rigorously assess the real-world utility of LuAna, an AI-powered platform for CXR interpretation developed in the public sector to assist general practitioners.

Despite ongoing debate about the advantages of SW-CRTs, including concerns about equipoise and delayed access to interventions [41], this design offers distinct benefits for implementation research. Governed by the same ethical principles as all clinical research [42], SW-CRTs are particularly valuable when evaluating innovations that are expected to be beneficial and for which withholding access may be contentious [42]. In the SUS context, this approach ensures that all centers ultimately gain access to AI support, promotes fairness and acceptability, and provides a pragmatic pathway to sustainable integration of the intervention into routine care.

The central goal is to determine whether LuAna improves clinicians’ ability to detect radiographic abnormalities, particularly in environments with limited access to radiology expertise. Comparisons against adjudicated, double-blinded radiologist interpretations will enable the quantification of diagnostic agreement, while stratified analyses by site type and physician characteristics will offer insights into contextual factors that may influence AI performance.

Importantly, the trial also investigates the clinical impact beyond diagnostic accuracy. By evaluating patient management decisions and turnaround times, we aim to capture how AI affects treatment pathways and efficiency in routine care. Usability assessments will provide critical feedback for refining and scaling the platform, thereby ensuring seamless integration into diverse clinical workflows across both mobile and desktop interfaces.

Robustness will be evaluated through sensitivity analyses on image quality, artifacts, and medical devices, thereby validating the model’s generalizability under real-world conditions. Additionally, longitudinal analysis of physician interpretations will explore whether repeated AI exposure improves independent performance, highlighting AI’s potential educational role.

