Beyond its methodological rigor, the LuAna trial advances an area in which robust evidence remains scarce: the real-world, prospective clinical evaluation of AI tools. While algorithmic performance is well documented in retrospective studies, few investigations have examined how AI behaves once deployed within the operational complexity of large, heterogeneous public health systems [40,43,44]. This gap has been repeatedly highlighted by international frameworks, including the DECIDE-AI (Developmental and Exploratory Clinical Investigation of Decision Support Systems Driven-Artificial Intelligence) guidelines, which emphasize the need for pragmatic, early-stage clinical evaluation before widescale deployment. Indeed, studies show positive primary outcomes for AI in clinical practice, but concerns remain due to mostly single-center trials, limited demographic data, and inconsistent reports on operational efficiency, which affect generalizability and practical use [45,46].

Evaluating AI-based decision-support systems involves several challenges: understanding their nature as complex interventions; considering user variability and the biases it introduces; integrating human factors into the collaboration between clinicians and AI; assessing both real patients and their data; dealing with continuous system changes; preventing the reproduction of health inequalities; ensuring that results generalize to different contexts; and guaranteeing reproducibility in the real world. By implementing LuAna across a nationally diverse range of health care settings, this study not only provides valuable empirical data on AI performance in real-world situations but also offers a unique opportunity to examine issues related to fairness [47-49].

Variability in patient demographics, imaging equipment, staffing, and workflow conditions across Brazil’s public health system creates a natural stress test for equity: the trial can assess whether AI-assisted interpretation benefits all subpopulations and settings equally or whether performance disparities emerge [50,51]. In doing so, it addresses 2 critical gaps in the global AI literature—real-world clinical validation and algorithmic fairness—offering evidence that is seldom available yet essential for responsible, scalable, and equitable integration of AI into routine care.

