### Limitations

Although the stepped-wedge design enhances real-world applicability by including diverse health care settings, the findings may still be influenced by context-specific factors, such as infrastructure, physician training, and patient demographics. Variation in image acquisition, whether from printed films, computer displays, or mobile capture, may introduce heterogeneity that affects both physician interpretation and algorithm performance. In addition, while the trial evaluates diagnostic accuracy, turnaround times, usability, and model robustness, it does not directly measure patient-level outcomes such as morbidity or mortality. Equity analyses are further limited by the narrow range of demographic variables collected, which may not fully capture socioeconomic or clinical determinants of performance. Finally, the lack of detailed clinical data, including comorbidities, treatment history, and laboratory findings, restricts the ability to contextualize radiographic interpretations and fully assess the AI integration into patient care pathways.

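### Demographics held only in aggregate cannot support the promised subgroup fairness assessment unless linked to each film; the physician localisation, management and turnaround claims also outrun the data described

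*Protocol article*

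**What the plan says.** **Demographics.** The Data Collection section says that "Only demographic variables, including age group, sex, and race, will be collected in aggregated form". The same sentence gives the purpose as "to characterize the study population and allow for fairness analyses, ensuring equitable and unbiased AI performance". The Discussion (Principal Findings) says that "the trial can assess whether AI-assisted interpretation benefits all subpopulations and settings equally" and presents algorithmic fairness as one of two gaps that the trial addresses. The Limitations section concedes that "Equity analyses are further limited by the narrow range of demographic variables collected"; it does not mention aggregation.

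**Localisation.** Under Secondary Outcomes: "Improvements in abnormality localization accuracy are also anticipated, both for the AI outputs alone and for physician interpretations after reviewing AI results". Textbox 1 lists no localisation outcome.

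**Management and turnaround.** Principal Findings states: "By evaluating patient management decisions and turnaround times, we aim to capture how AI affects treatment pathways". The Limitations section also counts turnaround among the things that the trial evaluates. Data Collection says that in the intervention group, after the physician's "clinical management, AI output (including probability scores and heatmaps) will be made available". The caption of Figure 2 says that control periods record the physician's interpretation only.

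**Ethics.** Under Ethical Considerations, the waiver of patient consent is justified because the study is "strictly observational and involves no intervention in routine clinical care, no modification of clinical management".

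**The concern.** Each of these claims needs a particular data item, and the article describes that item as absent, ambiguous or available in one phase only.

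The fairness claim matters most. Whether AI helps one demographic group less than another is a question about correct readings within that group, in each phase. The radiograph is the unit of analysis, so the group label must sit on the same record as the reading. If the wording is followed literally, the labels exist only as totals, and a headline equity conclusion would have no estimate behind it.

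The problem may also be irreversible. Collection began in January 2026, and patient identifiers are kept out of the research team's reach, so a label not stored with the film at capture may not be recoverable later.

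The other claims carry less weight. They would lead readers to expect a physician localisation result, and a randomised comparison of management and turnaround, that the described data do not clearly supply.

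**Working it through.** The plan gives no figure on this point to reproduce. The check sets the promised analyses beside the data items, with one illustration of what totals can identify.

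**1. Fairness: what unlinked totals identify.**

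Inputs: overall correct-reading rates of 67% (control) and 77% (AI-assisted), from the Statistical Analysis section. The subgroup's share *s* of films is an assumption, since the article gives none; it is taken as 0.5, 0.3 and 0.1, equal in both phases. Only totals per phase are assumed to be held.

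Let *a* be accuracy in the subgroup and *b* accuracy in the rest. The overall rate is *p* = *s·a* + (1 − *s*)·*b*, with *a* and *b* each between 0 and 1. Hence *a* lies between max(0, (*p* − (1 − *s*))/*s*) and min(1, *p*/*s*).

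For *s* = 0.5:
- Control: lower bound (0.67 − 0.5)/0.5 = 0.34; upper bound min(1, 1.34) = 1.
- AI: lower bound (0.77 − 0.5)/0.5 = 0.54; upper bound 1.
- Effect: from 0.54 − 1 = −0.46 to 1 − 0.34 = +0.66.

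| Share (assumed) | Control accuracy | AI accuracy | Possible AI effect in subgroup (percentage points) |
|---|---|---|---|
| 0.5 | 0.34 to 1 | 0.54 to 1 | −46 to +66 |
| 0.3 | 0 to 1 | 0.23 to 1 | −77 to +100 |
| 0.1 | 0 to 1 | 0 to 1 | −100 to +100 |

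Totals therefore do not show even the direction of a subgroup's benefit. With the category on each film record the problem disappears. Comparison by site or setting does not depend on these fields.

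**2. Physician localisation.** Data Collection lists three predefined questions for the first reading: normal or abnormal, each finding present or absent, and TB features. None asks for location. The reference-standard section defines a correct physician reading as a match on these binary classifications, and describes the radiologists' annotations as serving comparison with AI outputs. With the heatmaps, those annotations could support a localisation analysis for the AI alone. No physician location item is described.

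**3. Management and turnaround.** Neither appears in the primary outcome, Textbox 1 or the Statistical Analysis section. AI output follows management in the intervention phase, and control periods are said to record only the interpretation, so no control comparator for management is described. Intervention physicians do document their decision-making and any change after seeing the AI, which permits a before/after description within that phase. The platform logs all data automatically, so time stamps may exist in both phases, but no turnaround interval is defined.

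**4. Ethics text.** AI output after management, and no modification of management, agree with each other. Both sit uneasily with a stated aim to learn how AI affects treatment pathways. The observational label also sits uneasily with a randomised rollout in which physicians may revise readings.

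**The case against.** The strongest reply is that the aggregation wording is ambiguous. Age group is already a banded category, and the same sentence says that the data will serve fairness analyses, so the phrase may mean grouped categories stored per examination. A condensed article may leave record structure to the full protocol. This stands in part: a reader might infer that the subgroup analysis cannot be run at all, and the text does not establish that. Nor does it establish that fairness would shrink to a comparison among the 9 cities or 13 centres, because the level of aggregation is not stated. What remains is that the plain wording defeats the purpose given in the same sentence.

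On management and turnaround, a reader might infer that nothing is measured. The post-AI decision and change records and the automatic logging contradict that. The Figure 2 caption may also not be a full list of control-phase fields. Still, no such outcome is listed and no control comparator is described.

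On localisation, the three questions belong to the first reading, and the form for the final reading is not set out, so location might be captured there. Even then, the article describes no location data before AI or in control periods against which to show improvement.

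Finally, the primary outcome, primary model and sample size are untouched. That is correct and limits the seriousness of the point.

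**Conclusion.** The concern holds in a conditional form. Unless age group, sex and race are linked to each examination, the promised assessment of equal benefit across subpopulations cannot be made. The table shows the size of the gap for totals per phase; it rests on assumed subgroup shares and does not apply if banded categories are stored per film.

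The physician localisation claim is unsupported by the form and correctness rule as described; AI localisation is not affected. Management can be described only as before/after change within the intervention phase. Turnaround is undefined, and usable only if platform times are logged in both phases. The Figure 2 caption, Data Collection, Ethical Considerations, Principal Findings and Limitations need to be reconciled. No view is taken here on when AI output should be shown, and whether the waiver wording is acceptable is for the ethics committee.

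**What to change.** 1. State that age group, sex and race are stored as categories on each de-identified film record from now on. If they already are, replace the aggregation wording. Report the AI effect by subgroup as exploratory.
2. If films have been collected without the link, report how many and disclose this as a limitation.
3. Limit the localisation claim to AI outputs, or drop it.
4. Describe management only as recorded change before and after AI within the intervention phase, with no claim of a control comparison.
5. Define turnaround from platform time stamps in both phases, if these are logged, or remove it from Principal Findings and Limitations.
6. Reconcile the Figure 2 caption, Data Collection, Ethical Considerations, Principal Findings and Limitations with each other, and notify the ethics committee.

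The cost is at most three category fields in the app, a small privacy and ethics review, and text edits. Films already collected without the link may be unrecoverable, so the subgroup results may rest on only part of the sample.

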**Figure 2. F2:**
[figure not shown]
Study design and implementation flow of the LuAna (Lung Analysis) trial. The LuAna trial uses a batched stepped-wedge cluster-randomized design, where all centers begin in the control phase (gray) with physician-only interpretation. At randomly assigned sequences, clusters are grouped into batches and sequentially cross over to the intervention phase (green). Once a cluster transitions, it remains in the intervention phase until trial completion. At the site level, patient inclusion and physician interpretation occur continuously. During control periods, only the physician’s interpretation is recorded. During intervention periods, physicians first provide their interpretation, after which AI support (LuAna) is introduced. This design ensures staggered, overlapping transitions across centers while maintaining consistent trial procedures. AI: artificial intelligence.

All participating clusters will undergo a site initiation visit (SIV) prior to enrollment. All physician participants will complete the informed consent process and sign the informed consent form. During the SIV, local investigators will receive standardized training on study procedures, data entry, image capture protocols, and use of the study platform (LuAna). Training will include hands-on instruction to ensure the uniform application of inclusion criteria, proper anonymization of patient data, and completion of interpretation forms. Following the SIV, sites will begin patient recruitment and data collection. This study was registered on ClinicalTrials.gov (NCT06686251).

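### The article gives two sequences for showing the AI output; under one, non-AI information could reach only the intervention reading and be counted as AI effect

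*Protocol article*

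**What the plan says.** Three places in the protocol article describe when the physician sees the AI output.

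- **Figure 2 caption:** "During intervention periods, physicians first provide their interpretation, after which AI support (LuAna) is introduced".
- **Figure 3 caption:** the intervention steps are numbered. First, "physicians first perform an initial assessment of the CXR (1) and register their findings via the LuAna mobile app (2"; next, "After this, the AI model processes the image and returns a score and a heatmap highlighting abnormal regions (3" (the trailing numerals are the caption's step numbers). Step 4 is possible revision. Management is not among the steps.
- **Data Collection, paragraph on the reading questionnaire:** "In the intervention group, after the physician’s clinical management, AI output (including probability scores and heatmaps) will be made available". It continues: "Physicians will then document their final interpretation and decision-making process and subsequently record any changes made after reviewing the AI results".

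For control periods, the Figure 2 caption says: "During control periods, only the physician’s interpretation is recorded". The Objective in the abstract defines the primary outcome as accuracy with AI assistance against usual practice. Statistical Analysis specifies a logistic mixed model with fixed effects for intervention, calendar time, time since rollout and batch, and a random intercept for cluster.

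The section on reference standard and report return, with the Figure 4 caption, sends radiologist reports and critical-finding alerts back to the site. On data capture, Data Collection says: "All data will be automatically logged to enable auditing, reproducibility, and safety monitoring".

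**The concern.** The two sequences define different second readings. If AI output follows registration in one sitting, the second reading adds AI output and a second look at the film. If management comes between, the second reading may also draw on whatever the physician has learned since the first. Control films have no later entry through which such information could act.

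At stake is attribution. The trial is meant to estimate what AI adds to the physician's reading. A change caused by a returned report, a test result or the patient's course would be scored as an AI effect if it reached the final entry. Because it would begin at each cluster's crossover, it would coincide with the intervention indicator.

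**Working it through.** The article states no figure on this point that could be reproduced, so the check is mainly a comparison of passages, followed by short arithmetic.

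**1. Do the sequences agree?** Both captions give first reading, then AI, then possible revision. Data Collection gives first reading, management, AI, then final interpretation. Other sections do not settle it. Ethical Considerations says patient management is not changed by the study, while the Discussion says management decisions will be evaluated to show how AI affects treatment pathways. Each fits one sequence more easily than the other.

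**2. Which reading is scored?** The article does not name the entry. The Objective implies the AI-assisted one in intervention periods. In control periods there is only one.

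**3. Could non-AI information arrive in between?** One route is documented. Under Inclusion Criteria, a film has no existing report when it enters, and the LuAna Platform section says the image arrives together with the physician's report. The radiologist report should therefore follow the first reading in both arms. Nothing in the article closes the intervention arm's final reading before that report or an alert returns. How many films this touches is unclear: the Figure 4 caption speaks of final reports generally, while the text below it limits the use of patient identifiers to returning critical findings.

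**4. Can the primary model separate it?** None of its terms varies with when a film's final reading was entered. Calendar time and batch do not switch at a cluster's crossover. Time since rollout describes change after crossover, not a step at crossover. A timing effect therefore falls mainly on the intervention term.

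**5. What determines sign and size?** Let *s* be the share of intervention films with later information before the final reading, *c* the share of wrong first readings it corrects, and *h* the share of correct first readings it turns wrong. With the plan's 67% correct in control (33% wrong):

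bias = *s* × (0.33 × *c* − 0.67 × *h*)

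- Same session: *s* is about 0, so the bias is about 0.
- Break-even: *h* = (0.33 / 0.67) × *c* = 0.49 × *c*. If a quarter of errors were corrected, the bias would be negative once more than about 12% of correct readings were spoiled (0.49 × 0.25 = 0.12).
- A returned radiologist report comes from the readers who set the reference, so for that route *h* should be small and the sign positive.

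The documents give no value for *s*, *c* or *h*.

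**6. What would the sensitivity analysis cost?** Using the first reading for a share *L* of late intervention films removes the AI effect in those films. If the effect is the same in late and timely films, and first readings carry no AI effect, the estimate becomes 10 × (1 − *L*) points for the planned 10-point difference:

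- *L* = 10%: 10 × 0.90 = 9 points
- *L* = 30%: 10 × 0.70 = 7 points
- *L* = 50%: 10 × 0.50 = 5 points

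**The case against.** The captions give an order, not a time. They stay literally true if a management step lies between, so they may simply be condensed. Management may mean a decision taken in the same encounter, after which the AI output unlocks. The article ties revision to the AI output and says both pre-AI and post-AI readings are recorded. It does not say when a control reading is entered relative to management. Finally, the outcome is agreement with radiologists' reading of the image, so later clinical knowledge could also move a physician away from the reference.

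Much of this stands. A reader might infer that the captions show AI immediately after the first reading; they do not say so. A reader might also infer that control readings are always made before management; that is not stated. For test results and clinical course, the asymmetry is therefore a possibility rather than a fact.

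Three things remain. Condensation can explain a missing interval, but readers still have two workflows, one with a management step and one without. Recording both readings does not solve the problem, because their difference mixes AI with anything else learned in between. And the radiologist-report route does not depend on when control physicians act, since the report should follow the first reading in either arm.

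**Conclusion.** The point holds as an unreconciled sequence that leaves a possible bias in the primary contrast. Under the Data Collection text, the scored intervention reading is a later, post-management entry with no counterpart in control, and the primary model cannot distinguish AI from other information that reached it. This rests on the post-AI entry being the one scored, which the Objective implies, and on no unshown rule closing the final reading earlier.

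Two stronger readings are not supported. The first is that the bias necessarily favours AI: that is likely for a returned radiologist report, but not established for other information. The second is a definite size. Assuming, for example, that 10% to 30% of films are exposed and a quarter to a half of their errors are corrected gives 0.10 × 0.33 × 0.25 = 0.8 to 0.30 × 0.33 × 0.50 = 5.0 points. Those shares have no source in the documents, and the sum sets changes from right to wrong at zero. The size is unknown, and near zero if both readings are made in one session. The logged times can show which case applies.

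**What to change.** 1. Reconcile the Figure 2 caption, the Figure 3 caption and the Data Collection text on when the AI output is shown. No view is taken here on the clinical order.
2. Confirm that the platform logs, for each film, the times of first reading, AI display, final reading, and return of the radiologist report or alert. Report the first-to-final interval by city.
3. Pre-specify a sensitivity analysis of the primary outcome. For intervention films whose final reading was entered after the report or alert was returned, or beyond an interval fixed in advance, use the first reading. All films stay in their allocated group, consistent with the modified intention-to-treat rule.

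The cost is a wording change, one descriptive table and one extra model fit. No new data collection is needed if those times are logged, and the rule can be fixed before the analysis due by November 2026. The downside should be stated with the analysis: it removes genuine AI-driven revisions in late films, so it attenuates the effect in proportion to their share. It is a conservative bound beside the primary analysis, not a replacement, and should be read together with the share of late films.
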